# 7 STATISTICS AND DATA ANALYSES

## 7.1 METHOD OF RANDOMISATION

Once 12-16 men from a site are consented and recruited to the study, their details will be passed to SCTU for randomisation. We are aiming to recruit 16 men (8 per group). However, if having recruited for a period of two months, at least 12 men (6 per group) have been recruited, then randomisation will take place at this time. A computer-generated randomisation sequence will be created, allocating participants in a one-to-one ratio, stratified, with fixed block size, by

- Centre
- Disease status (curative versus palliative)

This process will be repeated for each cohort group so that allocation does not affect the allocation sequence of subsequent cohorts.

## 7.2 SAMPLE SIZE

We regard a  $\geq 1.5$  point difference in HFNS problem rating as clinically relevant. Based on similar interventions, this effect size is also considered realistic [4, 5]. To detect a  $\geq 1.5$  point difference in mean HFNS Problem Rating between CBT + TAU versus TAU alone at 6 months post-randomisation, with a standard deviation of 2.21 (32), 90% power and 5% type 1 error rate, requires a sample size of 94. The sample must also account for clustering introduced by the intervention (those attending the same CBT workshop may have more similar outcomes than those outside the group). Assuming 8 participants per group in the intervention, and intra-class correlation (ICC) of 0.01, requires 111 participants. An ICC of 0.01 is thought appropriate given the intervention is largely by self-management and smaller ICCs have been observed in similar studies [4]. The sample size increases to 150 (75/arm) allowing for 26% loss to follow-up (as per MENOS4).

A sample size of 150 corresponds to each site running four groups (2 per randomised arm), ensuring that a comprehensive process evaluation can be conducted. If each site recruits 4 patient groups, then each site

will recruit between 24 (6 per group) and 32 (8 per group) patients. Across 6 sites this leads to between 144 and 196 participants. An additional 7th site provides leeway with regards to reaching our recruitment target.

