| Sample Size:            | Between 144 and 192 patients                                                                                                                                                                                                                                                                                                                                                                                                                                                                                 |
| Treatment/Intervention: | A 4-week self-help treatment schedule with pre and post intervention virtual group workshops, delivered by the prostate cancer CNS team at week 1 and week 4. The intervention content comprises an instructional booklet including information and exercises addressing stress management, paced breathing and cognitive/behavioural strategies to improve wellbeing and for managing hot flushes, night sweats and sleep, and a CD demonstrating relaxation exercises.                                     |
| URL for Database:       | SCTU.MDSOL.COM                                                                                                                                                                                                                                                                                                                                                                                                                                                                                               |

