##### 3.1.3 Target population

MANCAN2 will recruit approximately 150 (144-192) men with prostate cancer currently receiving ADT and experiencing problematic HFNS symptoms (defined as a HFNS rating scale score of two or more). We will include patients receiving ADT in both the localised (curative) and advanced (palliative) settings with stratification for disease status. To minimise risk that patients might be symptomatic from their cancer, such that data integrity and outcomes might be influenced, we will recruit advanced disease patients only with hormone sensitive metastatic prostate cancer (excluding later stage castrate resistant disease).

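### Section 7.2: groups of 8 and an ICC of 0.01 do not turn 94 into 111, so the stated ICC, sample size and 90% power cannot all be right

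*Protocol*

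**What the plan says.** Section 7.2 builds the sample size in three steps.

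- **Before clustering.** For a difference of 1.5 points on the HFNS problem rating, the protocol works "with a standard deviation of 2.21 (32), 90% power and 5% type 1 error rate, requires a sample size of 94".
- **Clustering.** Men who attend the same CBT workshop may have more similar outcomes, so the section inflates the number: "Assuming 8 participants per group in the intervention, and intra-class correlation (ICC) of 0.01, requires 111 participants". It then defends 0.01 on two grounds: the intervention is mostly self-directed, and smaller ICCs have been seen in similar studies.
- **Loss to follow-up.** Allowing 26% loss, as in MENOS4, the target becomes 150, or 75 per arm.

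The section then turns to sites. Four groups of 6 to 8 men make 24 to 32 per site, and "Across 6 sites this leads to between 144 and 196 participants". The Trial Synopsis instead gives "Between 144 and 192 patients", and section 3.1.3 says "MANCAN2 will recruit approximately 150 (144-192) men with prostate cancer".

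In section 7.2 the effect size is cited to references 4 and 5, the SD to 32 and the ICC to 4.

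**The concern.** Groups of 8 with an ICC of 0.01 give a design effect of only 1.07, yet the protocol's inflation from 94 to 111 is about 18%. That gap is too large for rounding.

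The ICC is a central assumption here. Only one arm is delivered in groups, and section 7.3 fits therapy group as a random effect. If the ICC printed is not the ICC used, a reader cannot tell how much clustering the trial was planned to withstand, and the quoted 90% power is not the power of the design as described. Because section 7.3 promises CONSORT reporting, the calculation is likely to be repeated in the trial report.

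**Working it through.** **Inputs, all from section 7.2 unless noted:** difference 1.5; SD 2.21; power 90%; type 1 error 5%; group size m = 8; ICC 0.01; loss 26%; 1:1 allocation (section 7.1). Sidedness is not stated. Two-sided is assumed because it reproduces 94 and section 7.3 uses a 95% confidence interval.

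**1. The unclustered number reproduces.** In a two-sample t-test, 47 per arm gives power 0.902 and 46 per arm gives 0.896. So 2 × 47 = 94.

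**2. The loss step reproduces.** 111 / (1 − 0.26) = 150.0.

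**3. The clustering step does not.** The design effect is 1 + (m − 1) × ICC = 1 + 7 × 0.01 = 1.07.

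| Clustering | Calculation | Evaluable | Randomised (÷ 0.74) |
|---|---|---|---|
| CBT arm only, as the text describes | 47 × 1.07 = 50.3, so 51; 51 + 47 | 98 | 133 |
| Both arms | 94 × 1.07 = 100.6 | 101, or 102 with equal arms | 137-138 |
| Protocol | not shown | 111 | 150 |

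**4. What 111 would need.** The implied inflation is 111 / 94 = 1.181.

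- Both arms clustered: ICC = 0.181 / 7 = about 0.026.
- CBT arm only: ICC = 2 × 0.181 / 7 = about 0.052. An ICC of 0.05 gives 94 × (1 + 1.35) / 2 = 110.45, which rounds up to 111.

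**5. Other routes at ICC 0.01.**

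- Unequal group sizes (coefficient of variation 0.2 to 0.5) give 101-103 with both arms clustered.
- Satterthwaite degrees of freedom, which allow for the small number of groups, give 106 with the CBT arm only clustered and 116 with both.
- The closest route takes the 106 and rounds each arm up to seven whole groups of 8, giving 112. The protocol describes no such step, and the result is still not 111.

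**6. Power at 111 evaluable if ICC 0.01 is right, CBT arm only clustered.**

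- Dividing N by the average design effect (111 / 1.035 = 107.2) with a normal approximation gives 94%.
- For 56 CBT and 55 TAU, the variance of the difference is 2.21² × 1.07 / 56 + 2.21² / 55 = 0.0933 + 0.0888 = 0.182. The standard error is 0.427 and 1.5 / 0.427 = 3.51. With N − 2 degrees of freedom, power is 93.6%.
- With Satterthwaite degrees of freedom for seven CBT groups, the same split gives 91.7%.

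The range is therefore about 92-94%.

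**7. Site range.** 6 × 24 = 144 and 6 × 32 = 192, not 196. The synopsis and section 3.1.3 both have 192.

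**8. Citations.** In section 16, reference 4 is a survival paper in metastatic prostate cancer, 5 is a review of androgen deprivation and 32 describes an anxiety questionnaire. None fits the use made of it in section 7.2.

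**The case against.** The strongest defence is that the slip is harmless. Taking the ICC at its stated value, 111 evaluable exceeds the 98 needed, power is above 90%, and no man has to be added. The 192 is correct in two other places. This stands, and it limits the seriousness of the point. It does not rescue the calculation: the section states an ICC and defends it, and that ICC does not give the number beside it.

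Four stronger readings are tempting, and the protocol does not support them.

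- **That the ICC used was really 0.05.** It reproduces 111 when only the CBT arm is clustered, but so does about 0.026 in both arms. The text gives 0.01 twice and argues for it, which tells against a simple misprint.
- **That the trial is underpowered.** This needs assumptions the protocol does not make. With ICC 0.05 in the CBT arm, power at 111 is about 88-91%, depending on the split between arms and the degrees of freedom. With ICC 0.01 in both arms and small-cluster degrees of freedom, 112 evaluable would give about 89%. But section 7.2 places the clustering in the workshops, which TAU men do not attend.
- **That the lower limit of 144 falls short.** Section 7.2 names 150 as the sample size, obtains 144 from site logistics and adds a seventh site as a margin. Also, 144 × 0.74 = 106.6, about 107 evaluable, which exceeds the 98 to 102 from the design-effect calculation at ICC 0.01.
- **That no input can be traced.** Section 5.3.1.1 sources the 1.5 points to references 13 and 14, the two earlier CBT trials, and the 26% loss is attributed to MENOS4. The SD and the ICC are the inputs left without a usable source.

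**Conclusion.** Wrong as written, and it should be fixed. The fault lies in one step of the power calculation: at the stated inputs the requirement is 13 fewer than 111 with clustering in the CBT arm only, or 9 to 10 fewer with clustering in both. Either the ICC or the N is misstated, or an undescribed method was used. The protocol alone cannot settle which.

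The consequence depends on that answer. If 0.01 stands, the planned 150 is more than enough and power is understated by about 2 to 4 percentage points. If a larger ICC was used, the target may follow from it, but the printed 0.01 and the reasons given for it do not describe the design.

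This rests on a two-sided 5% test, groups of 8, the standard design effect and clustering in the CBT arm as section 7.2 describes. The 196 is a plain arithmetic slip, and the citation numbers are a separate defect that stops a reader from checking the SD and ICC.

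**What to change.** Amend section 7.2 as follows.

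- State the ICC actually used, the inflation formula and the arm or arms it applies to, so that ICC, N and power agree.
- If 0.01 stands, keep 150 and restate either the required N or the power, computed with degrees of freedom suited to the small number of CBT groups. If another ICC was used, print it and replace the sentence that justifies 0.01.
- Change 196 to 192, to match the synopsis and section 3.1.3.
- Correct the citations for the effect size, the SD and the ICC. The last two matter most, because nothing else in the protocol sources them.

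The cost is a wording change at the next amendment and a short recalculation. No change to enrolment, sites or data collection is needed.

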### **7.3 PRIMARY AND SECONDARY ANALYSES**

The primary outcome measure, HFNS Rating Scale compared to baseline, will be compared between the CBT intervention + TAU arms at 6 months post randomisation. Difference in HFNS Rating Scale between the two groups will be analysed using a linear mixed model, adjusting for baseline HFNS Rating Scale and stratification factors. Therapy group will be included in the model as a random effect. Interpretation of the effect of the intervention will be based on the regression coefficient for group and corresponding 95% confidence interval. Secondary outcomes at 6 weeks and 6 months post-randomisation will be analysed similarly, accounting for stratification factors and clustering.

Analyses will be based on a modified intention-to-treat sample (i.e. excluding participants not contributing data). This will be supported by an analysis that deals with missing data should missingness lead to >10% of the sample being excluded. Methods may involve either multiple imputation using chained equations, or full information maximum likelihood.

MANCAN2 will be analysed according to the principles of the International Conference on Harmonisation E9 guidelines and reported using Consolidated Standards of Reporting Trials (CONSORT). A full statistical analysis plan (SAP) will be developed prior to the final analysis.

### **7.4 HEALTH ECONOMIC ANALYSES**

The economic analysis will take an NHS perspective to estimate both cost effectiveness (£ per change in HFRS) and cost utility (Incremental £/QALY) as well as a budget impact. QALYs will be estimated from EORTC using the SCHARR algorithm (<https://www.sheffield.ac.uk/scharr/sections/heds/mvh/cancer>).

Costs will include that of the intervention and on any changes in use of NHS services. As the intervention cost might differ between that in the trial and in routine practice, we will take two approaches, one detailing changes in CNS team total time allocations in each arm during the trial, and another collecting data on views of both the CNS team and managers on the extent to which the intervention could be incorporated into standard practice (and under what circumstances such as being included in training and in guidelines). While both these costs will be reported, the latter would be more relevant in estimating budget impact if implemented in routine practice. The cost of changes in service use will be based on a customised resource use patient questionnaire at 6 weeks and 6 months.

Estimates of both cost and QALY increments will be estimated for each patient and incorporated into the planned statistical analyses described above. If a clinically relevant gain in the primary outcome is found to be statistically significant, more detailed economic modelling will be carried out, to explore uncertainty and to extend the time frame beyond that of the trial. This will build on the recent cost effectiveness modelling for similar interventions for hot flushes in breast cancer.[39]

All relevant resource items identified will be costed using published national cost data (British National Formulary and Personal Social Services Research Unit, and NHS reference cost). Accumulated costs and QALYs per patient will be estimated by means of area under the curve. Where appropriate we will estimate incremental cost-effectiveness ratios (ICERs). We will estimate mean values and 95% percentiles using non-parametric bootstrapping. We will produce cost-effectiveness acceptability curves (CEACs) to illustrate the uncertainty of such estimates. Major assumptions made in the costing and QALYs will be tested by means of sensitivity analyses.

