#### **1) NHS**

Data on the use of medication, primary care visits, and out-patient visits will be collected using the Resource Use Questionnaire. In addition, we will estimate out-of-pocket spending such as herbal remedies, acupuncture or alternative therapies and time off work due to HFNS. The cost of the intervention will be based on nurse logs to record staff training cost, and time to deliver the intervention. This information will be used for sensitivity analysis from a societal perspective. We will use an adapted form of the Client Service Receipt Inventory.[38] Intervention-specific resource use will be collected through nurse logs to record staff training cost, and time to deliver the intervention.

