#### **2) Participants**

Data will be collected on all participants about other actions that they may be taking to manage their HFNS, including yoga, acupuncture or other behavioural activities (see section 7.4). Collection of such information from each participant will be through questionnaire sent by mail at 6 weeks and 6 months. QoL will be measured by EORTC-QLQ-C30 and will be collected at baseline, 6 weeks and 6 months.

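### Section 7.4 assigns area under the curve to costs as well as QALYs; costs reported over periods and one-off intervention costs should be summed

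*Protocol*

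**What the plan says.** Protocol section 7.4 gives one rule for two quantities: "Accumulated costs and QALYs per patient will be estimated by means of area under the curve".

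On the cost data, the same section says: "The cost of changes in service use will be based on a customised resource use patient questionnaire at 6 weeks and 6 months". Section 5.3.3, under Participants, gives the same two time points for what men do to manage their symptoms: "Collection of such information from each participant will be through questionnaire sent by mail at 6 weeks and 6 months". In Table 1 the resource-use questionnaire is marked at weeks 6 and 26 and not at baseline. Neither Table 1 nor the text states what recall period each questionnaire covers.

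The intervention cost comes from a different source. Section 5.3.3, under NHS, says: "The cost of the intervention will be based on nurse logs to record staff training cost, and time to deliver the intervention". Section 7.4 counts this cost among the costs to be analysed.

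For QALYs, the EORTC QLQ-C30 is collected at baseline, 6 weeks and 6 months, so a utility curve has all three of its points.

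**The concern.** Utility is a level at a moment. Integrating it over time gives a quantity in quality-adjusted years, which is what is wanted. A questionnaire cost is already an amount accrued over a period, and a training or workshop cost is an amount incurred once. The total of such amounts is their sum. Joining them as points on a curve and taking the area answers a different question.

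The planned data would not define such a curve either. Without a resource-use measurement at baseline, the segment from 0 to 6 weeks has no starting value, so the analyst would have to invent one. Intervention cost has no place on the curve, because it is logged as it arises and not measured at 6 weeks or 6 months.

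What is at stake is the cost difference between the arms, and with it the ICER and the acceptability curve. CBT cost arises in one arm only and falls early: section 5.3 has the programme ideally starting 3 weeks after randomisation and lasting 4 weeks. A rule that weights early and late costs differently therefore need not cancel between arms.

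**Working it through.** **Inputs.** Cost time points of 6 and 26 weeks, with none at baseline (Table 1, section 7.4). Intervention cost from nurse logs (section 5.3.3). The economic section states no cost figure, so there is nothing of the plan's own to reproduce.

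**Assumptions.** Recall covers weeks 0–6 (cost c1) and weeks 6–26 (cost c2) without overlap. The area is taken by the trapezoid rule. The pound amounts are illustrative.

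**Correct total for service use:** c1 + c2.

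**Area on weekly cost rates.** The rate at week 6 is r1 = c1/6 and at week 26 is r2 = c2/20. With starting rate r0:

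Area = ½(r0 + r1) × 6 + ½(r1 + r2) × 20 = 3·r0 + 13·r1 + 10·r2

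- If r0 = 0: area = (13/6)·c1 + (10/20)·c2 = 2.167·c1 + 0.5·c2.
- If r0 is set equal to the week-6 rate: area = (16/6)·c1 + 0.5·c2 = 2.667·c1 + 0.5·c2.

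| c1 (£) | c2 (£) | Sum (£) | Area, zero start (£) | Area, start at week-6 rate (£) |
|---|---|---|---|---|
| 100 | 400 | 500 | 216.7 + 200 = 417 | 266.7 + 200 = 467 |
| 200 | 300 | 500 | 433.3 + 150 = 583 | 533.3 + 150 = 683 |
| 300 | 200 | 500 | 650 + 100 = 750 | 800 + 100 = 900 |
| 60 | 200 | 260 | 130 + 100 = 230 | 160 + 100 = 260 |

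The first three rows have the same true total and differ only in timing. The last row has a constant weekly rate (£10). There the area equals the sum, but only if the starting rate is set to match.

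**Area on the raw amounts, time in years, zero start.** ½·c1·(6/52) + ½(c1 + c2)·(20/52) = (13·c1 + 10·c2)/52. For £300 and £200 this is (3,900 + 2,000)/52 = 113.5, in pound-years. It is not a cost.

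**Effect on the difference between arms.** With zero start the rule is linear, so the error in the incremental cost is 1.167·Δ1 − 0.5·Δ2, where Δ1 and Δ2 are the true between-arm differences in the two periods.

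- A one-off £100 in the CBT arm, placed in weeks 0–6, counts as £217 with zero start and £267 with a start at the week-6 rate.
- A £100 saving in weeks 6–26 counts as £50.
- Both together have a true increment of £0. With zero start the area gives 216.7 − 50 = £167 against the intervention.

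**The case against.** The best defence is that the sentence is loose drafting. It does not say trapezoid. The area under a stepwise cost rate, constant within each period, equals the sum of the period costs exactly and needs no baseline value. The word for accumulation in the sentence also fits summation. This is fair, but it concedes the point: on that reading the rule is summation, and the protocol should say so. As written, one method covers both quantities, and for utilities at three time points an analyst would normally use the trapezoid.

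A second defence is that section 5.3.3 announces a combined statistical and health economic analysis plan, which is not among the documents reviewed. That would excuse a missing detail. Here the rule is stated, and a plan that follows the protocol would inherit it.

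Third, the size of the error depends on recall periods that the protocol does not give, and the economic evaluation runs only if the intervention proves effective. Both are true. The first limits the figures to illustrations. The second means that the rule matters exactly when the economic result would be used.

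Two stronger readings are tempting and are not supported:

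- A reader might infer that the bootstrap resamples individual men and so ignores cost shared within therapy groups. Section 7.4 says only "We will estimate mean values and 95% percentiles using non-parametric bootstrapping" and names no resampling unit. It also says "Estimates of both cost and QALY increments will be estimated for each patient and incorporated into the planned statistical analyses described above", and section 7.3 says of those analyses "Therapy group will be included in the model as a random effect". The unit can properly be left to the combined plan. Delivery cost is not wholly shared either, since section 4.5 offers one-to-one telephone sessions.
- A reader might infer that the budget impact will be wrong. Section 7.4 treats the second costing approach, based on the views of the CNS team and managers, as the more relevant one for that purpose.

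**Conclusion.** The point holds for costs only. Section 7.4 fixes a method that is right for QALYs and unsuited to costs, and the planned cost data (two questionnaires, no baseline, nurse logs) do not define a cost curve.

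Under the assumed recall periods and a trapezoid with zero start, early costs carry a weight of 2.167 and later costs a weight of 0.5, where both should be 1. The total can come out too low or too high depending only on timing. With other recall periods or another starting value the weights change. Area and sum agree only in special cases or under a stepwise reading. It cannot be said that the ICER will be wrong, only that the rule as written can distort it. The primary clinical analysis is not affected. This is a correction that should be made to a secondary, conditional analysis.

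**What to change.** Replace the single sentence in section 7.4, and carry the change into the combined analysis plan, with wording such as:

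*Area under the curve will be used for QALYs. Cost per patient will be the sum of intervention cost (nurse logs) and costed resource use over the non-overlapping periods 0–6 weeks and 6 weeks–6 months.*

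State the recall period of each questionnaire alongside, so that the two periods can be seen neither to overlap nor to leave a gap. The change takes two sentences and needs no new data, visits or participants.
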